### 7.2.3 Dose Modifications for Sorafenib-Associated Hypertension

***Hypertension is a known and potentially serious adverse event associated with sorafenib treatment. Patients will have their blood pressure monitored and recorded weekly during the first 6 weeks of therapy***

| Grade (CTCAE v3.0)                                                                                                                                                                                                                                                                                                                                                                                                                                                                 | Antihypertensive Therapy                                                                                                                                                | Blood Pressure Monitoring                                                                                                                               | Sorafenib Dose                                                                                                            |
|------------------------------------------------------------------------------------------------------------------------------------------------------------------------------------------------------------------------------------------------------------------------------------------------------------------------------------------------------------------------------------------------------------------------------------------------------------------------------------|-------------------------------------------------------------------------------------------------------------------------------------------------------------------------|---------------------------------------------------------------------------------------------------------------------------------------------------------|---------------------------------------------------------------------------------------------------------------------------|
| Grade 1                                                                                                                                                                                                                                                                                                                                                                                                                                                                            | None                                                                                                                                                                    | Routine                                                                                                                                                 | No change                                                                                                                 |
| Grade 2 (asymptomatic)                                                                                                                                                                                                                                                                                                                                                                                                                                                             | Initiate monotherapy (suggest dihydropyridine calcium-channel blocker)                                                                                                  | Increase frequency and monitor (by health professional) every 2 days until stabilized                                                                   | No change                                                                                                                 |
| Grade 2 (symptomatic/persistent)
OR
Diastolic BP > 110 mm Hg
OR
Grade 3                                                                                                                                                                                                                                                                                                                                                                                  | Add agent(s):
Ca ++ channel blocker (if not already used),
K + channel opener (angiotensin blockers),
beta-blocker,
thiazide diuretic | Increase frequency and monitor (by health professional) every 2 days until stabilized; continue qod monitoring to stabilization after dosing restarted. | Hold* sorafenib until symptoms resolve and diastolic BP < 100 mm/Hg.

Resume treatment at 1 dose level lower |
| Grade 4                                                                                                                                                                                                                                                                                                                                                                                                                                                                            |                                                                                                                                                                         |                                                                                                                                                         | Off protocol therapy                                                                                                      |
| * Patients requiring a delay of > 21 days should go off protocol therapy                                                                                                                                                                                                                                                                                                                                                                                                           |                                                                                                                                                                         |                                                                                                                                                         |                                                                                                                           |
| CTCAE v3.0 definitions
Grade 1: asymptomatic, transient (<24 hrs) increase by > 20 mmHg (diastolic) or > 150/100 if previously WNL; intervention not indicated
Grade 2: recurrent or persistent (>24 hrs) or symptomatic increase by >20 mmHg (diastolic) or to >150/100 if previously WNL; monotherapy may be indicated.
Grade 3: requiring more than one drug or more intensive therapy than previously
Grade 4: life threatening (e.g., hypertensive crisis) |                                                                                                                                                                         |                                                                                                                                                         |                                                                                                                           |

### 7.2.4 Dose Modifications for Other Sorafenib-Associated Toxicity

| Toxicity               | Grade 1                          | Grade 2                          | Grade 3*                                                                                                       | Grade 4*                                                                                      |
|------------------------|----------------------------------|----------------------------------|----------------------------------------------------------------------------------------------------------------|-----------------------------------------------------------------------------------------------|
| Non-hematologic | Continue at the same dose level. | Continue at the same dose level. | Withhold dose until toxicity is grade ≤1, then resume treatment at the same dose level. If patient experiences | Withhold dose until toxicity is grade ≤1, then reduce one dose level and resume treatment, or |

|                    |                                  |                                  |                                                                                                                                                                                                                                                            |                                                                                                                                                                                                                   |
|--------------------|----------------------------------|----------------------------------|------------------------------------------------------------------------------------------------------------------------------------------------------------------------------------------------------------------------------------------------------------|-------------------------------------------------------------------------------------------------------------------------------------------------------------------------------------------------------------------|
|                    |                                  |                                  | a second grade 3 toxicity, withhold dose until toxicity is grade $\leq 1$ , then reduce one dose level and resume treatment.                                                                                                                               | discontinue at the discretion of the principal investigator.                                                                                                                                                      |
| Hematologic | Continue at the same dose level. | Continue at the same dose level. | Withhold dose until toxicity is grade $\leq 2$ , then resume treatment at the same dose level. If patient experiences a second grade 3 toxicity, withhold dose until toxicity is grade $\leq 2$ , then reduce dose to 400 mg p.o. qd and resume treatment. | Withhold dose until toxicity is grade $\leq 2$ , then reduce dose to 400 mg p.o. qd and resume treatment, or discontinue at the discretion of the principal investigator after discussion with study supporter. . |

\*Patients who develop grade 3 fever/chills, grade 3 elevation of hepatic transaminases with ALT and AST  $<10\times$  ULN, grade 3 hyperlipasemia or hyperamylasemia without clinical or other evidence of pancreatitis, grade 3 leukopenia, or grade 3/grade 4 lymphopenia may continue study treatment without interruption at the discretion of the investigator.

Because certain grade 3-4 adverse events may occur with radiotherapy, the above table should be modified for these adverse events as defined below (unless the adverse events are definitely attributable only to sorafenib, in which case refer to above table). Attribution to sorafenib at least in-part should be present in order to justify sorafenib dose-reduction:

- Neutropenia – Grade 3 or Grade 4 lasting  $\leq 7$  days: no action. Grade 4 lasting  $>7$  days: refer to table above
- Neutropenic Fever – Grade 3 lasting  $\leq 5$  days: no action. Grade 3 lasting  $>5$  days or Grade 4: refer to table above
- Leukopenia – No dose reduction
- Thombocytopenia -- Grade 3: no action. Grade 4: refer to table above. Grade 3-4 with clinically significant bleeding: treat as Grade 4
- Anemia – Grade 3: no action. Grade 4: refer to table above
- Nausea/Vomiting – Per above table, only if persistent Grade 3-4 despite maximal anti-emetic adjustment
- Fatigue – Grade 3: no action. Grade 4: refer to table above.
- Diarrhea – Diarrhea should be initially managed with anti-diarrhea agents including loperamide or Lomotil. If persistent Grade 3- 4 toxicity, refer to table above.

- Hypophosphatemia – Grade 3: replacement therapy. Grade 4: refer to above table only if refractory to replacement therapy

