#### 4.0 ACCRUAL GOAL

- Phase I— Dose-escalation schedule comprising 6 to 12 patients (see schema). This sample size is based on a traditional 3+3 cohort design with escalating doses of sorafenib in combination with 50 Gy of conformal radiotherapy delivered in 25 fractions (200 cGy per fraction). Based on preclinical data regarding the radiobiology of sorafenib, sorafenib will be initiated at a dose of 200 mg twice daily, followed by 200 mg Q AM/400 mg Q PM for the 2nd cohort, followed by 400 mg bid for the 3rd cohort. Since 400 mg bid is the well established MTD for sorafenib monotherapy in patients with renal cell carcinoma and hepatocellular carcinoma, the dose will not be escalated above this level even if DLT is not observed. Dose level escalation will be determined based on DLTs observed from initiation of sorafenib/RT until time of surgery.
- Phase II— anticipated number of 25 patients will be enrolled depending on phase I result. Anticipating an improvement in near-complete pathological response ( $\geq 95\%$  tumor necrosis) from 0% with RT alone to 33% with combined sorafenib and RT, we will have an 80% power to detect this difference if we accrue 25 patients, assuming a type I error rate of 5%.

Total target accrual is 30-35 patients depending on results of dose-escalation schedule from Phase I of trial.

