## 7.2 Sorafenib Dose Modification

7.2.1 General Considerations. According to the following dose level table, sorafenib dosing will be modified for adverse events that are at least in-part *attributable* to sorafenib according to the following sections.

| Dose Level | Sorafenib            |
|------------|----------------------|
| 0*         | 200 mg daily         |
| 1          | 200 mg twice daily   |
| 2          | 200mg am
400mg pm |
| 3          | 400 mg twice daily   |

\*Patients will be removed from protocol treatment if dose reduction below this level is indicated.

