| Grade 3
Moist desquamation, ulceration, blistering or severe pain of the hands or feet, or severe discomfort that causes the patient to be unable to work or perform activities of daily living | First occurrence           | 
Institute supportive measures such as topical therapy for symptomatic relief and interrupt sorafenib treatment for a minimum of 7 days and until toxicity has resolved to grade 0–1
 
 
• When resuming treatment after dose interruption, decrease sorafenib by one dose level
 
• If toxicity is maintained at grade 0–1 at reduced dose for a minimum of 7 days and up to 28 days, increase by one dose level
 
                                                                                                                                                                                                                                                                                                                                                                               |
|                                                                                                                                                                                                    | Second occurrence          | As for first occurrence. Upon resuming sorafenib treatment, decrease dose by one dose level.
Decision whether to dose re-escalate should be made based on clinical judgment and patient preference.                                                                                                                                                                                                                                                                                                                                                                                                                                                                                                                                                                                                                                                     |

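### Section 7.2.4 sets the reduced sorafenib dose for hematologic toxicity at a fixed 400 mg once daily, which is no reduction for a patient already on 400 mg/day, the Phase I starting dose

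*Protocol*

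**What the plan says.** Protocol section 7.2.1 gives the general rule: "According to the following dose level table, sorafenib dosing will be modified for adverse events". Its table has four levels: level 0, 200 mg daily; level 1, 200 mg twice daily; level 2, 200 mg in the morning and 400 mg in the evening; level 3, 400 mg twice daily. A footnote to level 0 sets the floor: "Patients will be removed from protocol treatment if dose reduction below this level is indicated".

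The other reduction rules move the patient down relative to the current level:

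- Hand-foot skin reaction, grade 3 (7.2.2): "When resuming treatment after dose interruption, decrease sorafenib by one dose level".
- Hypertension (7.2.3): "Resume treatment at 1 dose level lower".
- Non-hematologic toxicity, grade 4 (7.2.4): "then reduce one dose level and resume treatment".

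The hematologic row of 7.2.4 does not. Both its second-grade-3 cell and its grade 4 cell say to withhold until grade 2 or lower, "then reduce dose to 400 mg p.o. qd and resume treatment". The grade 4 cell also allows discontinuation at the investigator's discretion; the grade 3 cell does not.

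The bullets below the table narrow the trigger. For thrombocytopenia they read "Grade 3: no action. Grade 4: refer to table above. Grade 3-4 with clinically significant bleeding: treat as Grade 4". Grade 4 anemia and grade 4 neutropenia lasting more than 7 days are also sent to the table.

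Section 4.0 fixes the Phase I start: "sorafenib will be initiated at a dose of 200 mg twice daily".

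**The concern.** A rule meant to lower the dose should do so at every level where it can be triggered. A fixed target works only for patients above it. Level 1 already delivers 400 mg/day, so the instruction changes the schedule from twice to once daily, doubles each single administration from 200 to 400 mg, and leaves the daily total unchanged.

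Level 1 is not a remote case. It is the first Phase I cohort, it becomes the Phase II dose if it proves to be the MTD, and it is where a level 2 patient lands after a one-level cut for hand-foot reaction or hypertension.

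The qualifying events are serious and largely overlap the DLT definition in section 7.1. A patient could therefore have a DLT on the starting dose and resume the same daily dose under a rule that calls for a reduction. The stake is individual patient safety and consistent dosing between investigators, not the trial's inference.

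**Working it through.** **Inputs.** The daily totals follow from the 7.2.1 table: level 0, 200 mg; level 1, 2 × 200 = 400 mg; level 2, 200 + 400 = 600 mg; level 3, 2 × 400 = 800 mg. The hematologic target in 7.2.4 is 400 mg once daily, or 400 mg/day.

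**Change in daily dose** = target ÷ current − 1.

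| Current level | Current mg/day | 7.2.4 as written | Per-level targets (see fix) | Uniform one-level cut |
|---|---|---|---|---|
| 3 | 800 | 400 (−50%) | 400 (−50%) | 600 (−25%) |
| 2 | 600 | 400 (−33%) | 400 (−33%) | 400 (−33%) |
| 1 | 400 | 400 (0%) | 200 (−50%) | 200 (−50%) |
| 0 | 200 | 400 (+100%) | off protocol treatment | off protocol treatment |

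As written, the rule reduces the dose at levels 3 and 2, does nothing at level 1, and raises it at level 0, against the table's footnote.

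**Which events reach the cells.** The bullets give no action for grade 3 neutropenia, grade 3 anemia and grade 3 thrombocytopenia without significant bleeding, unless the event is definitely attributable to sorafenib alone. The second-grade-3 cell is therefore rarely reached. The grade 4 cell remains live for grade 4 neutropenia beyond 7 days, grade 4 thrombocytopenia (or grade 3–4 with significant bleeding) and grade 4 anemia.

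**How often.** Section 8.1 gives only any-grade bands for sorafenib monotherapy. Thrombocytopenia is in the 1% to below 10% band; anemia and neutropenia are not listed. Expected any-grade thrombocytopenia cases:

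- 3 to 6 level 1 patients in Phase I: 3 × 0.01 = 0.03 to below 6 × 0.10 = 0.6.
- 25 Phase II patients, if level 1 is the MTD: 25 × 0.01 = 0.25 to below 25 × 0.10 = 2.5.

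Grade 4 or bleeding cases are a subset, and rates with radiotherapy may differ. The protocol gives no rate for qualifying events. For illustration, assume 0.5% to 5% per patient. The chance of at least one is then:

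- n = 3 to 6: 1 − 0.995³ = 1.5% to 1 − 0.95⁶ = 26.5%.
- n = 25: 1 − 0.995²⁵ = 11.8% to 1 − 0.95²⁵ = 72.3%.

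**Exposure after resumption.** Section 7.4 puts treatment at about 35 days. If the cell applies between day 7 and day 21 and the drug is held 7 to 14 days (both assumed), the days left run from 35 − 7 − 7 = 21 down to 35 − 21 − 14 = 0. For neutropenia the upper end is below 21, because grade 4 must first last more than 7 days.

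**The case against.** The best reply is that section 7.2.1 governs. The cell says to reduce, so a sensible investigator would read it as presuming a patient above 400 mg/day and would use the level table and its floor for anyone else. Nobody would double a level 0 dose under the name of a reduction. The route is also narrow: the patient must be at or below 400 mg/day, have a qualifying event at least partly attributed to sorafenib, recover within three weeks, not be discontinued, and still have treatment days left. The qualifying events mostly count as DLTs, so Phase I escalation already responds to them. On this view the point is a wording correction.

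Much of that stands. The harm is limited, and most sites would probably notice the anomaly. The upper ends of the illustrative probabilities are generous: 5% for grade 4 or bleeding events would be at least half of the any-grade thrombocytopenia ceiling, and the 72.3% also needs level 1 to be the MTD.

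The reply does not make the instruction right. A general table does not cure a specific cell that contradicts it, and section 7.2.1 itself sends the reader to the sections that follow. Withholding, optional discontinuation and section 7.7 decide whether dosing resumes, not at what dose. Counting a DLT protects later cohorts, not the patient who had it.

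**Conclusion.** The concern holds. The hematologic cells of 7.2.4 name a regimen outside the governing dose table. It gives a 0% cut in daily dose at level 1, the Phase I starting dose, and read literally a 100% increase at level 0. At levels 3 and 2 it works (−50% and −33%). This follows from the protocol's own text and needs no assumption.

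The number of patients affected is likely small, but the protocol does not give a qualifying-event rate to fix it; the probabilities and remaining days above rest on stated assumptions and the conclusion does not depend on them. MTD determination, power and the primary endpoint are essentially unaffected. It should be corrected because it is a patient-safety instruction that fails at the starting dose and is easily repaired.

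**What to change.** In both hematologic cells of 7.2.4, replace the fixed dose with a target for each current level, using the 7.2.1 labels:

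- Level 3 or level 2: resume at level 1 (200 mg twice daily, 400 mg/day).
- Level 1: resume at level 0 (200 mg daily).
- Level 0: off protocol treatment, as the 7.2.1 footnote already provides.

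This keeps the existing 400 mg/day target at levels 3 and 2 and adds a real cut at level 1. A uniform one-level reduction would be simpler and would match the other rules. It would, however, soften the level 3 cut from −50% to −25%, so it is suitable only if the sponsor accepts that.

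The cost is two table cells in an amendment, with no effect on sample size or analysis.
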